D. When each institution confirms that eligible subjects are hospitalized as planned and there is no change to the eligibility (change of surgery method, etc.), the institution shall notify KGOG accordingly and request randomization. KGOG will access the eCRF System (Redcap), input the data on the eligibility sheet and perform randomization. Random numbers will be assigned in the form of ‘R_XX_01’ where XX is the initials of the institutions.

D. Randomization table is created in advance and embedded in the eCRF system. The randomization table is created in advance by the Medical Research Cooperation Center of Seoul National University Bundang Hospital and will be imported to the eCRF system directly without the involvement of investigators. Details of the randomization table are as follows:

A) The ratio of SS-PDS experimental group vs. control group is 1:1

B) The ratio of subcutaneous drainage experimental group vs. control group is 1:1

C) Stratification factors are institutions and BMI (≤30 vs >30), Surgery indication (Confirmed or suspected cancer vs not). The Stratification factors are applied to all of A), B), and random.

D) Block randomization

(5) Notification of randomization results

A. Randomization results should not be notified until just before the fascia closure begins during surgery.

B. Just before the fascia closure begins, each institution will notify the screening number to KGOG by phone and check the randomization result by phone as well.

C. Randomization results will not be notified using numbers such as 0 or 1 but in the form of ‘SS-PDS experimental group’ or ‘subcutaneous drain control group.’ After being notified of the randomization results, each institution will say out the result again to KGOG so as to avoid any error.

D. KGOG will create a record on the eCRF according to random number and inform the pair of screening number-randomization number to each institution so that the institution can input data on the eCRF.

(6) Nondisclosure of randomization results

A. SS-PDS randomization results

A) Study subjects are not notified of the randomization results.

B) In order to minimize investigator influence on the randomization at the time of incisional hernia diagnosis, randomization results are not recoded on medical records but only on CRF.

B. Subcutaneous drain randomization results

Randomization results are disclosed

(7) Undisclosed randomization results are disclosed to:

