A. investigators: investigators at each institution can view CRF and check randomization results without a separate approval procedure.

B. study subjects: if investigators see it necessary for medical purposes, they can inform the subjects of the randomization results after approval by the principal investigator.

(8) Interim Analysis

A. Interim analysis for the initial safety review

A) When the 10th subject is allocated to A+B arm and finishes his/her Week 4 visit, an evaluation will be performed on 10 subjects in A+B arm for incidence, types, and grades of surgical site infections, wound dehiscence, and other adverse events.

B) Evaluation results will be reported to IRB. If incidence, types, and grades of adverse events are judged to exceed the usual range, possible measures including trial discontinuation will be considered.

B. Interim analysis for wound dehiscence of subcutaneous drain

A) An evaluation will be performed when the 44th subject of A+C arm and B+D arm, respectively, completes his/her week 4 visit.

B) If wound dehiscence incidence of A+C arm is lower than B+D arm (one-sided p < 0.005), it will be decided that subcutaneous drain insertion reduces wound dehiscence and further randomization will be stopped. That is to say that subcutaneous drain will be inserted to all subject from then.

1. **Investigational Product Dosage, Application/Administration Methods, Combination Therapy, and Reasons for Comparator (as applicable)**

(1) SS-PDS arm (fascia closure using SS-PDS)

A. Instructions

A) STRATAFIX Symmetric PDS Plus, suture size: 1/0, suture length: 45cm, needle size: 40mm (CT needle) (Ethicon, Somerville, NJ, USA)

B) Running suture will be used as recommended by the manufacturer and stated in previous studies [PMID: 28603661] (<https://www.youtube.com/watch?v=PTYtYvSaGMg>, <https://youtu.be/TPyulS4fQgQ>)

C) Peritoneum closure should be performed. If peritoneum closure is impossible due to peritoneotomy, it may not be performed.

D) For fascia closure, stiches will be made 5-8 mm apart including 5-8 mm thick tissues on both sides of the incision surface.

E) It is allowed to make additional stiches for fascia closure with a few interrupted sutures using PDS or other sutures based on the investigator’s judgment.

F) Suture length is recommended to be 4 times longer than the skin incision. That is, if the skin incision is 20cm, it is recommended to use 80cm or longer suture for closure.

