| Compare cumulative wound dehiscence incidence at Week 4 after surgery between A+B arm and C+D arm. | Cumulative incidence of wound dehiscence of A+B arm will be compared with that of C+D arm using chi-square or Fisher's exact test. P value 0.05 will be used to determine significance. | Patients who undergo surgery and complete week 4 visit |
| Compare wound dehiscence incidence at Week 4 after surgery between A+B arm and C+D arm. | Incidence of wound dehiscence of A+B arm will be compared with that of C+D arm using chi-square or Fisher's exact test. P value 0.05 will be used to determine significance. | Patients who undergo surgery and complete week 4 visit |
| Compare BPI-K scores that are obtained at baseline, Day 2 and Day 4 after surgery between A+B arm and C+D arm. | BPI score (total and each question) obtained at baseline will be compared between A+B vs C+D arm. BPI score (total and each question) obtained at postoperative day 2 will be compared between A+B vs C+D arm. BPI score (total and each question) obtained at postoperative day 4 will be compared between A+B vs C+D arm. Student t-test will be used. P value 0.05 will be used to determine significance. If BPI score at baseline is imbalanced between arms, change of BPI score (from baseline to postoperative day 2, 4) will be compared. | Patient who undergo surgery and complete BPI |
| Compare NRS pain scores collected until Day 4 after surgery between A+B arm and C+D arm. | NRS collected for postoperative 4 days will be compared between A+B vs C+D arm using linear mixed model. P value 0.05 will be used to determine significance. | Patients who undergo surgery and NRS are measured |
| Compare cumulative incidence and types of surgical site infections until Day 4 after surgery between A+C arm and B+D arm (depending on whether subcutaneous drain is inserted or not) | Cumulative incidence of SSI of A+C arm will be compared with that of B+D arm using chi-square or Fisher's exact test. P value 0.05 will be used to determine significance. Type of SSI will be summarized. | Patients who undergo surgery |
| Compare cumulative wound dehiscence incidence at Week 4 after surgery between A+C arm and B+D arm (depending on whether subcutaneous drain is inserted or not) | Cumulative incidence of wound dehiscence of A+C arm will be compared with that of B+D arm using chi-square or Fisher's exact test. P value 0.05 will be used to determine significance. | Patients who undergo surgery and complete week 4 visit |

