| Compare wound dehiscence incidence at Week 4 between A+C arm and B+D arm (depending on whether subcutaneous drain is inserted or not) | Incidence of wound dehiscence of A+C arm will be compared with that of B+D arm using chi-square or Fisher's exact test. P value 0.05 will be used to determine significance. | Patients who undergo surgery and complete week 4 visit |
| Incidence, types, grades and relevance of adverse events excluding incisional hernia, pains, surgical site infections, and wound dehiscence. | Incidence, type and grade of adverse events except incisional hernia, pain, SSI, wound dehiscence will be summarized using appropriate metrics. They will be compared using appropriate statistical methods. | Patients who undergo surgery. |

1. **Distinctions from conventional treatments and studies**

(1) Using barbed suture for abdominal fascial closure falls within the range of treatments approved by US FDA and Korea MFDS.

(2) Using barbed suture for abdominal fascial closure has a possibility to reduce potential incisional hernia.

(3) There is a lack of systematical studies for abdominal fascial closures using barbed suture.

1. **Benefits for and Risks to Subjects**

(1) Predictable side effects/risks and countermeasures

A. Regardless of predictable side effects/risks – causality,

this trial targets female patients who undergo midline laparotomy. Therefore, various adverse events involved with surgery may be observed. Also, a considerable number of subjects are expected to be diagnosed as and treated for malignant tumor, and adverse events may be observed in this regard.

A) Blood and lymphatic system disorders: anemia, febrile neutropenia, hemolysis, leukocytosis

B) Cardiac disorders: palpitations, sinus bradycardia

C) Ear and labyrinth disorders: vertigo

D) Eye disorders: Blurred vision, conjunctivitis, dry eye

E) Gastrointestinal disorders: abdominal distension, abdominal pain, anal pain, ascites, bloating, constipation, diarrhea, dry mouth, dyspepsia, enterocolitis, fecal incontinence, flatulence, ileus, intra-abdominal hemorrhage, nausea, vomiting

F) General disorders and administration site conditions: chills, edema face, edema limb, fatigue, fever, infusion related reaction, infusion site extravasation, irritability, localized edema, non-cardiac chest pain, pain

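### If the drain interim rule fires, later patients all receive a drain but stay in the final A+C vs B+D cohorts, so the drain comparison is confounded with calendar period

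*Protocol*

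**What the plan says.** Protocol, Control Group Setting and Randomization, sets the drain allocation: "The ratio of subcutaneous drainage experimental group vs. control group is 1:1". Under (8) Interim Analysis, B, the timing is: "An evaluation will be performed when the 44th subject of A+C arm and B+D arm, respectively, completes his/her week 4 visit". The trigger is "If wound dehiscence incidence of A+C arm is lower than B+D arm (one-sided p < 0.005"). On a crossing, the drain is declared effective against dehiscence, "further randomization will be stopped", and "subcutaneous drain will be inserted to all subject from then".

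The table under Efficacy Evaluation Standards, Evaluation Methods has three drain rows:
- Surgical site infection: the cohort is "Patients who undergo surgery".
- Cumulative dehiscence: "Cumulative incidence of wound dehiscence of A+C arm will be compared with that of B+D arm using chi-square or Fisher's exact test", in operated patients who completed the Week 4 visit.
- Dehiscence at Week 4: "Incidence of wound dehiscence of A+C arm will be compared with that of B+D arm using chi-square or Fisher's exact test", in the same cohort.

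All three rows describe the contrast by whether a subcutaneous drain is inserted. None limits the cohort to patients randomised before a stop or includes a period term. The protocol does not say that the interim result replaces the final drain analysis.

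**The concern.** The stopping rule and the analysis cohorts are each clear, but they do not fit together. After a crossing, every later patient has a drain by default and none can enter the no-drain side. If these patients are counted by drain status, A+C mixes early randomised patients with late unrandomised ones, while B+D holds early patients only. Any change over time in site mix, case mix, surgical experience or wound care is then read as a drain effect, in either direction.

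At stake are secondary objectives G (surgical site infection) and H (dehiscence). Infection is the more exposed, because it does not trigger the stop and its only planned drain test is the final one. The primary hernia comparison, A+B vs C+D, stays randomised provided that only drain randomisation stops.

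**Working it through.** **Inputs from the protocol.** Total 174 (Target Sample Size); 44 per drain group at the look and one-sided p < 0.005 (Interim Analysis, B); 9 patients per month (Trial Schedule); Week 4 visit accepted at 3 to 5 weeks (Observation Items). The protocol gives no sample size, power or event rate for the drain comparison, so all drain event rates below are assumptions.

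**The plan's own figure.** The total comes from the suture comparison. The arcsine formula with 0.13 vs 0.03, one-sided 0.05 and power 0.80 gives 81.5 per arm. Dividing by 1 − 0.06 gives 86.7, so 87 per arm and 174 in all. The point here uses only the total.

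**Counts after a crossing.**
1. While the last of the 88 patients awaits Week 4, about one month's enrolment (9) is randomised: 88 + 9 = 97, or about 49 vs 48.
2. Enrolled later: 174 − 97 = 77, all with a drain.
3. Final contrast: 49 + 77 = 126 vs 48. Never randomised to drain: 77/126 = 61%.
4. Range: with nobody enrolled in the waiting period, 44 + 86 = 130 vs 44 (86/130 = 66%). With 10 enrolled, 49 + 76 = 125 vs 49 (76/125 = 61%).

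**Size of the period bias.** The expected pooled A+C rate is (49 × early drain rate + 77 × later drain rate)/126. Pooling therefore shifts the A+C rate by (77/126) × (later − early) = 0.61 × the change over time. A fall from 20% to 15% shifts it by 3.1 points, and a fall to 10% by 6.1 points, with no drain effect at all.

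**Infection after a crossing.** This is a two-sided chi-square test at 0.05, 126 vs 48, with no drain effect on infection, an early rate of 20%, and infection independent of dehiscence. The rates are conditional on the stop having occurred.

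| Later background rate | Rejection, as written |
|---|---|
| 20% | 5.3% |
| 15% | 9.1% |
| 10% | 19.6% |
| 30% | 12.3% |

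Limited to patients randomised before the stop, the rate stays near 5% whatever the later rate.

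**Dehiscence along the actual path.** Look at 44 vs 44 (chi-square, z > 2.576). If crossed, pool 126 vs 48; otherwise continue 1:1 to 87 vs 87. With no drain effect and an early rate of 20%, the look crosses in 0.44% of trials. Overall two-sided rejection lies between about 4.5% and 5.2% for later rates from 5% to 30%, with pooling or with the restriction.

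**Dehiscence when the drain works.** Assume early rates of 10% vs 25% (true difference 15 points) and a later drain rate of 20%. The look crosses in about 22% of trials. In those trials the pooled difference averages 16.2 points and the randomised-only difference 24.6. The gap is 8.4 points, of which 0.61 × 10 = 6.1 is change over time. The remaining 2.3 is dilution of early results that were selected by crossing the boundary.

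**The case against.** The strongest reply is that arms A to D are randomised arms. A patient given a drain by default after randomisation stops belongs to none of them, and the dehiscence question is declared settled at the look. On that reading the final drain analysis is already limited to randomised patients, and an SAP could say so. It is true that the protocol never states that later patients are coded A or C. But the cohorts are defined by having had surgery, the contrast is labelled by drain insertion, and nothing excludes later patients. The protocol has fixed the cohorts itself, and the literal reading includes them.

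Two stronger readings are tempting and should be set aside.
- A reader might infer that the drain test has a false-positive rate near 20%. That figure appears only if the 126 vs 48 split is imposed on every trial. For dehiscence, the split follows a crossing, which is very rare when the drain does nothing.
- A reader might take the 24.6-point randomised-only average as the truth that pooling dilutes. The assumed truth is 15 points. The 24.6 is inflated by early stopping, and that the pooled 16.2 lies near 15 is an accident of the assumed drift.

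The scope is also limited: secondary objectives only, and only after a crossing.

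**Conclusion.** The point holds as period confounding on a contingent branch. If the rule fires, the stated cohorts give about 126 vs 48, with about 61% of the drain side never randomised to drain. The estimates for objectives G and H then absorb about 0.61 of any change over time in the drained patients' rate.

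For dehiscence the damage is to the estimate, not to the overall type I error. For surgical site infection the test itself loses protection: about 9% to 20% false rejection after a crossing for a fall from 20% to 15% or 10%, to the extent that infection is independent of dehiscence. How often this arises depends on the unknown drain effect: about 0.4% of trials with none, and about 22% at 10% vs 25%. Both crossing rates use the chi-square statistic; Fisher's test, which the rule does not exclude, would cross less often. The counts follow from the protocol's own figures, while the event rates and drifts are assumptions. The primary comparison is not affected. The change is worth making because it is cheap and must be settled before the look.

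**What to change.** Add to (8) Interim Analysis, B, and to each A+C vs B+D row: drain comparisons use only patients randomised to drain or no drain before drain randomisation stopped, analysed as randomised and including those still awaiting Week 4 at the look. Later patients are described separately and stay in all A+B vs C+D comparisons.

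In the same place, say that the randomisation that stops is the drain randomisation only, since the present sentence does not name the factor. Note also that after an early stop the restricted dehiscence estimate is biased upward by the stopping rule, so that it is reported with that caution.

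The cost is a few sentences. If the rule fires, the final drain comparison has about 97 patients instead of 174 and is correspondingly less precise. If it does not fire, nothing changes.

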**2) Trial Hypothesis and Purpose**

(1) Schema

[figure not shown]

(2) Primary Objective

The purpose of this trial is to verify the hypothesis: ‘In comparison to sutures without barbs, using SS-PDS for abdominal fascia closure on female patients who undergo incisional hernia in midline laparotomy due to gynecological diseases will reduce the cumulative incidence of incisional hernia for 1 year after surgery.’

(3) Secondary Objective

A. Compare the incidence curves of incisional hernia over time between A+B arms and C+D arms (depending on whether SS-PDS is used or not).

B. Compare cumulative incidence and types of surgical site infections up to 4 weeks after surgery between A+B arms and C+D arms (depending on whether SS-PDS is used or not).

C. Compare incidence and cumulative incidence of wound dehiscence at Week 4 after surgery between A+B arms and C+D arms.

D. Compare BPI-K scores that are obtained on Day 2 after surgery between A+B arms and C+D arms (depending on whether SS-PDS is used or not)

E. Compare BPI-K scores that are obtained on Day 4 after surgery between A+B arms and C+D arms (depending on whether SS-PDS is used or not)

F. Compare NRS scores that are collected until Day 4 after surgery between A+B arms and C+D arms (depending on whether SS-PDS is used or not)

G. Compare cumulative incidence of surgical site infections and their types until Week 4 after surgery between A+C arms and B+D arms (depending on whether subcutaneous drain was used or not)

H. Compare incidence and cumulative incidence of wound dehiscence between A+C arms and B+D arms at Week 4 after surgery (depending on whether subcutaneous drain was used or not).

I. Compare incidence of adverse events, their type and relevance excluding incisional hernia, pains, surgical site infections, and wound dehiscence between A+B arms and C+D arms.

J. Create a surgical video of abdominal fascia closure using SS-PDS.

1. **Code Names (or Generic Names of Principal Components) of Investigational Product and Medical Device, Raw Material Quantities, Formulation and etc. (including** **comparator)**

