| 4-week cumulative incidence of wound dehiscence after surgery | Subjects are advised to make outpatient visits for Week 4 after surgery. Visits made between 3 to 5 weeks after surgery can be counted as Week 4 visit. Investigators will conduct a physical checkup to diagnose wound dehiscence. Wound dehiscence is defined as all wound dehiscence in any depth and length. If subjects make outpatient visits before Week 4 after surgery, investigators should check for wound dehiscence. All information obtained from visits made immediately after surgery up to Week 4 will be used to calculate all cumulative incidence. Events that will be included in the calculation of cumulative incidence will be: when wound dehiscence is observed even just once until Week 4 after surgery; when removal of stapler or suture is impossible at Week 4; or wound dehiscence is observed during follow-up after stapler or suture was removed at Week 4. |
| Wound dehiscence incidence at week 4 after surgery | Subjects are advised to make outpatient visits for Week 4 after surgery. Visits made between 3 to 5 weeks after surgery can be counted as Week 4 visit. Investigators will conduct a physical checkup to diagnose wound dehiscence. Wound dehiscence at Week 4 is defined as: when a wound is expanded at Week 4 evaluation; when removal of stapler or suture is impossible; or wound dehiscence is observed during follow-up after stapler or suture was removed at Week 4. If wound dehiscence was observed before Week 4 but it disappeared at Week 4, the subject is not counted to have wound dehiscence at Week 4 after surgery. When stapler or suture is removed at Week 4 visit, a follow-up visit or phone counseling is required. If no wound dehiscence is discovered from the follow-up visit or phone counseling, the subject is not counted to have wound dehiscence. However, if wound dehiscence is discovered from the follow-up visit or phone counseling, the subject is counted to have wound dehiscence. |
| BPI-K Score | BPI-Korean version is used at baseline, Day 2 and Day 4 after surgery. |
| NRS Pain Score | Pain scores, measured by NRS which is a usual way of monitoring surgical patients, and record times are collected from immediately after surgery until 10pm of Day 4 after surgery. |

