| Demographics of subjects, surgical information | Date of birth, height, weight, current smoker, medical history, pre- and postoperative chemotherapy, corticosteroids, previous abdominal surgery, ASA classification, type of surgery, suture length, wound length, operation time, antibiotic prophylaxis, intra-abdominal drain, subcutaneous drain, DVT prophylaxis, Patient controlled analgesia (Y/N, type IV or epidural), wound anesthetics infiltration system, perioperative complications, transfusion, postoperative radiation, ICU care |
| Incidence, types, grades and relevance of adverse events excluding incisional hernia, pains, surgical site infections, and wound dehiscence | Adverse events are collected by listening to the subject’s medical history and conducting a physical checkup during hospitalization for surgery, Week 4 and Year 1 visits after surgery. All visits and medical records until Year 1 after surgery will be used. CTCAE ver 4.0 will be used to grade each adverse event. |

1. **Efficacy Evaluation Standards, Evaluation Methods**

| Purpose | Analysis and Evaluation Methods | Cohorts for analysis |
| --- | --- | --- |
| Compare cumulative incisional hernia incidence until Year 1 after surgery between A+B arm and C+D arm. | Cumulative incidence of incisional hernia of A+B arm will be compared with that of C+D arm using chi-square or Fisher's exact test. P value 0.05 will be used to determine significance. | All patients who undergo surgery. Patients who do not have incisional hernia will be censored at last visit. Incidence will be estimated from time-occurrence curve. |
| Compare incisional hernia incidence curve by time between A+B arm and C+D arm. | Time-occurrence curve of incisional hernia will be depicted using Kaplan-Meier method and be compared between A+B vs C+D arm using log-rank test. P value 0.05 will be used to determine significance. | All patients who undergo surgery |
| Compare cumulative incidence of surgical site infections and their types until Week 4 after surgery between A+B arm and C+D arm. | Cumulative incidence of SSI of A+B arm will be compared with that of C+D arm using chi-square or Fisher's exact test. P value 0.05 will be used to determine significance. Type of SSI will be summarized. | Patients who undergo surgery |

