G) Infections and infestations: abdominal infection, bladder infection, catheter related infection, peritoneal infection, pharyngitis, stoma site infection, urinary tract infection, wound infection

H) Injury, poisoning and procedural complications: intraoperative gastrointestinal injury, intraoperative venous injury, intraoperative urinary injury, large intestinal anastomotic leak, postoperative hemorrhage, wound complication, wound dehiscence

I) Investigations: activated partial thromboplastin time prolonged, alanine aminotransferase increased, alkaline phosphatase increased, aspartate aminotransferase increased, platelet count decreased, urine output decreased, weight gain, weight loss

J) Metabolism and nutrition disorders: anorexia, dehydration

K) Musculoskeletal and connective tissue disorders: back pain, flank pain, myalgia, neck pain

L) Psychiatric disorders: anxiety, delirium, insomnia

M) Renal and urinary disorders: hematuria, proteinuria, urinary frequency, urinary incontinence, urinary retention, urinary urgency

N) Reproductive system and breast disorders: menorrhagia, irregular menstruation, pelvic pain, vaginal discharge, vaginal dryness, vaginal hemorrhage

O) Respiratory, thoracic and mediastinal disorders: atelectasis, cough, dyspnea, hypoxia, pleural effusion, sore throat

P) Skin and subcutaneous tissue disorders: alopecia, pruritus, purpura, urticarial

Q) Vascular disorders: flushing, hot flashes, phlebitis, thromboembolic event

B. Side effects/risks from using barbed suture and countermeasures

A) Side effects/risks

Barbed suture has been used for various soft-tissue closures since years ago. SS-PDS is approved to be used for abdominal fascia closure. However, there are little clinical experience of using SS-PDS for abdominal fascia closure. Potential side effects/risks would include increased incisional hernia, surgical site infections, wound dehiscence and pain but increase is not expected.

B) Countermeasures

When the 10th subject is allocated to the A+B arm and completes his/her week 4 visit, an evaluation will be performed on 10 subjects in A+B arm for surgical site infections, wound dehiscence and incidence, types and grades of other adverse events. Evaluation results will be reported to IRB. If incidence, types, and grades of adverse events are judged to exceed the usual range, possible measures including trial discontinuation will be considered.

C. Side effects/risks from using subcutaneous drain and countermeasures

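### Wound dehiscence is pooled across all depths for the fascial-suture comparison, and the protocol is inconsistent on whether it is graded

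*Protocol*

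**What the plan says.** **Definition.** Under Observation Items, the cumulative 4-week item states: "Wound dehiscence is defined as all wound dehiscence in any depth and length". A patient counts "when wound dehiscence is observed even just once until Week 4 after surgery". The separate Week 4 item counts a patient "when a wound is expanded at Week 4 evaluation; when removal of stapler or suture is impossible", or when dehiscence appears after staple or suture removal. Neither item names a tissue layer. The table Efficacy Evaluation Standards, Evaluation Methods tests both as binary outcomes by chi-square or Fisher's exact test, for A+B versus C+D and again for A+C versus B+D.

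**Objective.** Secondary objective C reads: "Compare incidence and cumulative incidence of wound dehiscence at Week 4 after surgery between A+B arms and C+D arms". Objective H asks the same of the drain arms. For surgical site infection, by contrast, the objectives ask for types, and Observation Items names the CDC standards for them.

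**Grading.** The first interim analysis, under Control Group Setting and Randomization (8) A, evaluates 10 A+B subjects for "incidence, types, and grades of surgical site infections, wound dehiscence, and other adverse events". The only grading scale is in the adverse-event row of Observation Items: "CTCAE ver 4.0 will be used to grade each adverse event". That row is headed "Incidence, types, grades and relevance of adverse events excluding incisional hernia, pains, surgical site infections, and wound dehiscence". Objective I and the adverse-event row of the efficacy table carry the same exclusion. Benefits for and Risks to Subjects restates the 10-subject review as covering "surgical site infections, wound dehiscence and incidence, types and grades of other adverse events".

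**Promised comparison.** The Safety Assessment row of the Overview promises a comparison of adverse-event grade between the suture groups.

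**The concern.** The test suture closes fascia; the drain lies in the subcutaneous layer. One any-depth variable suits the drain question better than the suture question. In the suture comparison, a short skin gap and a fascial separation each count as one event, and superficial events can outnumber fascial ones.

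The safety side matters more. Benefits for and Risks to Subjects names increased dehiscence as a potential risk of the test suture and makes the 10-subject review the countermeasure. That review may lead to discontinuation on the basis of incidence, type and grade. If no scale applies to dehiscence, reviewers cannot report its grade consistently.

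The hernia endpoint may also miss an early fascial failure. Under Removal of subjects from study, item D, another midline laparotomy leads to withdrawal without further follow-up, and Observation Items censors such a patient for hernia. A fascial dehiscence re-operated through the midline could therefore leave the primary endpoint uncounted. If this happens before Week 4, the patient may also fall outside the dehiscence cohort, which requires a completed Week 4 visit. Item F keeps the data collected up to withdrawal, but without a depth field those data need not show that the tested closure failed.

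**Working it through.** **1. Where dehiscence is graded.**

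| Protocol section | Dehiscence graded? | Arms compared |
| --- | --- | --- |
| Overview, Safety Assessment | Promises adverse-event grade; dehiscence not mentioned | Suture groups |
| Objective I | Excluded | A+B vs C+D |
| Interim Analysis (8) A | Yes | None (10 A+B subjects) |
| Observation Items, adverse-event row (CTCAE 4.0) | Excluded | None |
| Efficacy table, adverse-event row | Excluded | Not stated |
| Benefits and Risks, restated review | Grades tied to other adverse events | None (10 A+B subjects) |
| Safety section, (2) Evaluation Methods, grade 3 or above | Exclusion not repeated | A+C vs B+D |

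The two wordings of the same review differ. The one grade comparison that might include dehiscence names the drain arms. No row compares dehiscence grade between A+B and C+D.

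**2. Size of the dilution.** The protocol gives no dehiscence rate, so there is no stated figure to reproduce for this endpoint. The one document input is sample size: 87 per arm with 6% drop-out leaves 87 × 0.94 = 81.8, about 82. (The 87 itself reproduces for hernia at 0.13 versus 0.03, one-sided 0.05, power 0.80, by the arcsine formula: h = 0.3896; n = 2 × ((1.645 + 0.842)/0.3896)² = 81.5; 81.5/0.94 = 86.7.)

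Assumptions: any-depth dehiscence in controls 10% or 20%; fascial dehiscence 1% in controls and 3% with the test suture; the superficial rate is equal in both arms, and fascial and superficial cases add.

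- Pooled endpoint: 9% + 1% = 10% against 9% + 3% = 12%; or 19% + 1% = 20% against 19% + 3% = 22%.
- Superficial share of counted events: 9/10 = 90% and 19/20 = 95% in controls; 9/12 = 75% and 19/22 = 86% with the test suture.

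Power at two-sided 0.05 ≈ Φ[(d − 1.96·SE₀)/SE₁], where SE₀ = √(2p̄(1−p̄)/n) and SE₁ = √((p₁(1−p₁) + p₂(1−p₂))/n).

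- 10% vs 12%: SE₀ = 0.0489, SE₁ = 0.0488; (0.02 − 0.0958)/0.0488 = −1.55; power 6%.
- 20% vs 22%: SE₀ = SE₁ = 0.0636; (0.02 − 0.1247)/0.0636 = −1.65; power 5%.
- Fisher's exact test, by enumerating the two binomials, gives about 4% in both cases.

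**3. Would a fascial-only test do better?** Expected fascial events are 82 × 0.01 = 0.8 and 82 × 0.03 = 2.5. Fisher power, by the same enumeration, is about 2%. The large-sample formula would give 15%, but it is unreliable at such counts.

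**4. The 10-subject review.** The chance of at least one fascial event is 1 − 0.99¹⁰ = 10% at a 1% rate and 1 − 0.97¹⁰ = 26% at 3%.

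**The case against.** Objective C promises only incidence, and the definition and test deliver that. An inclusive definition is explicit, easy to apply at a physical examination, and suits the drain objective and the drain interim analysis. Types are promised for infection and not for dehiscence, so the contrast with infection reflects different objectives. All of this stands: the definition is a weak choice for the suture contrast, not an error.

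A reader might infer that grades of dehiscence do not exist at all. The protocol does not support that. One wording of the review ties grades only to other adverse events, dehiscence is listed among the predictable adverse events, and the grade 3 or above comparisons do not repeat the exclusion. The exclusion itself may only be meant to avoid counting an endpoint twice. The eCRF, which could hold depth or grade, is not shown. What remains is an inconsistency between sections, with no scale assigned to dehiscence in the protocol.

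The grade 3 or above comparisons do not settle the matter for the suture arms, because they name A+C versus B+D.

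A reader might also infer that a depth field would make a rise in fascial failure detectable. With about one event against two or three, it would not. The low power reflects trial size as well as mixing of depths.

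Finally, the primary endpoint addresses fascial failure through hernia, including hernia before Week 4, and serious unexpected suture-related events are reported within 7 days. This lowers the stakes, though a dehiscence re-operated through the midline can still be censored from the hernia endpoint.

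**Conclusion.** The point holds in two limited parts. First, objective C as defined cannot separate fascial from superficial dehiscence. Under the assumed rates, a tripling of fascial dehiscence shifts the analysed endpoint by 2 percentage points, with about 4-6% power. All the rates are assumptions, and the result illustrates dilution only. Second, the protocol asks for dehiscence grades in one place, excludes dehiscence from the only graded item in others, and restates the same review differently. As written, no section compares dehiscence grade between the suture arms, despite the Overview's promise on adverse-event grade.

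This is a matter of secondary-endpoint and safety definition. It does not touch the primary analysis or the sample size, and it does not show that early fascial failure would go unseen. The improvement is worth making because it is cheap and lets the safety review report what the interim section asks of it.

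**What to change.** - At the examinations already planned, record for each dehiscence its depth (skin or subcutaneous only, versus fascial) and its CTCAE grade.
- Keep the any-depth endpoint for objectives C and H.
- Add a descriptive report of fascial dehiscence and of grade 3 or above dehiscence, by A+B versus C+D and in the 10-subject review.
- Reconcile Interim Analysis (8) A, the adverse-event rows of Observation Items and of the efficacy table, the restated review in Benefits for and Risks to Subjects, and the safety Evaluation Methods on whether dehiscence is graded. In the last of these, also reconcile the arms named with the suture-group comparison promised in the Overview.

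The cost is two eCRF fields and some editing. Fascial events will be too few for a meaningful test, so these figures should be presented as counts without a claim of significance.
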